### Delay to Final DAS28-CRP Calculation

As the DAS28-CRP calculation includes the CRP blood test result, the final DAS28-CRP score can only be fully calculated when the CRP result is available (ie, after conclusion of each study visit). Partial DAS28-CRP scores can be calculated at the time of the study visit and are usually indicative of final flare or remission status. However, it is possible that unexpected elevation of the CRP result may push the final DAS28-CRP score above the remission threshold and thus change the flare or remission status after the study visit has been completed. If this occurs at the baseline visit, then the patient would become ineligible to continue and should be withdrawn from the study at this point. If this occurs at a follow-up visit, the patient will continue with the Axivity AX6 and RA-FQ monitoring and follow-up schedule that was arranged in their recently completed study visit. Any necessary changes to clinical management will be arranged by the ROADMAP clinical team as per usual clinical care.

### Clinical Discretion

It is possible for DAS28-CRP scores to be elevated by events unrelated to inflammatory arthritis: for example, by a concurrent infection causing an elevation of CRP, or trauma causing a painful or swollen joint. The study investigator has discretion to discount such false elevations of the DAS28-CRP and follow the remission section for the relevant study visit if felt to be appropriate. In such cases, it is expected that the study investigator’s decision should match that of the ROADMAP service clinician; for example, if a patient with concurrent infection had an elevated DAS28-CRP, but the ROADMAP clinician considered their arthritis to still be in remission, then the study investigator should manage the patient as being in remission.

### Adverse Events and Serious Adverse Events

#### Adverse Event

An AE is defined as any untoward medical occurrence experienced by the patient during their participation within the study. The severity of AEs is defined as follows:

Mild: Symptoms noted but no disruption to normal daily activitiesModerate: Symptoms sufficient to disrupt normal daily activitiesSevere: Symptoms sufficient to prevent normal daily activities

#### Causality

All AEs should be assessed by the principal investigator or their medically qualified delegate for any causal relationship with a study procedure, namely, remote electronic patient-reported outcome measure (ePROM) or activity/physiological monitoring. Causality is defined in Table 1.

**Table 1. T1:** Categories for assessing the causal relationship between an adverse event and trial medication.

Relationship	Description
Unrelated	There is no evidence of any causal relationship.
Unlikely	There is little evidence to suggest there is a causal relationship (eg, the event did not occur within a reasonable time after administration of the trial procedure). There is another reasonable explanation for the event (eg, the patient’s clinical condition, other concomitant treatment).
Possible	There is some evidence to suggest a causal relationship (eg, because the event occurs within a reasonable time after administration of the trial procedure). However, the influence of other factors may have contributed to the event (eg, the patient’s clinical condition, other concomitant treatments).
Probable	There is evidence to suggest a causal relationship and the influence of other factors is unlikely.
Definitely	There is clear evidence to suggest a causal relationship, and other possible contributing factors can be ruled out.
Not assessable	There is insufficient or incomplete evidence to make a clinical judgment of the causal relationship.

#### Serious Adverse Event

A serious adverse event (SAE) is any AE that results in death, is life-threatening (meaning the patient was at risk of death at the time of the event, not that the event might hypothetically have caused death if it had been more severe), requires hospitalization or prolongation of existing hospitalization, results in persistent or significant disability or incapacity, or is a congenital anomaly or birth defect. Clinical judgment should also be used to determine seriousness in other situations, and important AEs or reactions that are not immediately life-threatening and do not result in death or hospitalization but may jeopardize the patient or require intervention to prevent one of the outcomes listed above should also be classified as serious.

#### Expected Symptoms

This study will recruit patients with active RA, and as such are expected to have joint pain, joint swelling, joint stiffness, and fatigue, especially in the event of an arthritis flare.

#### Protocol Specifications

Joint pain, joint swelling, joint stiffness, and fatigue will not be recorded as an AE. An AE will not be classified as an SAE if it is a hospitalization, surgical procedure, or other medical intervention (whether as an inpatient, day-case, outpatient, or in primary care) that was planned before the recruitment of the patient to the study.

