## Methods

### Study Design

This prospective, single-center observational cohort study is embedded within the ROADMAP DMARD tapering clinic at Freeman Hospital, Newcastle upon Tyne, United Kingdom (Multimedia Appendix 1). Adults with clinician-confirmed RA in remission who are undergoing or are about to begin DMARD tapering will be followed for 9 months. Continuous wrist-worn accelerometry and weekly RA-FQ responses will be collected throughout follow-up, with clinical assessments aligned with routine ROADMAP visits at baseline and approximately months 3, 6, 9, and 12 together with ad hoc visits for suspected flare.

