**Inclusion criteria**
Clinical diagnosis of rheumatoid arthritis (RA) made by a consultant rheumatologist28-joint Disease Activity Score with C-reactive protein (DAS28-CRP)<2.4 at point of enrollment to the studyCurrent (or expected within the next 28 days) tapering of a disease-modifying antirheumatic drug (DMARD; conventional synthetic, targeted synthetic, or biologic)Able to walk at least 4 m independently without walking aidsPatient willing to commit to complete remote Rheumatoid Arthritis Flare Questionnaire (RA-FQ) and continuously wear monitoring devices

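### The AE rule excludes joint symptoms and fatigue whatever their cause, so wrist joint symptoms caused by the device cannot become AEs; the adjoining text wrongly describes the cohort as having active RA

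*Protocol article*

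**What the plan says.** All places are in the protocol article.

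- **Expected Symptoms** describes the cohort and what follows for symptoms: "This study will recruit patients with active RA, and as such are expected to have joint pain, joint swelling, joint stiffness, and fatigue". It adds that this applies especially in a flare.
- **Protocol Specifications**, the next section, lists the same four symptoms: "Joint pain, joint swelling, joint stiffness, and fatigue will not be recorded as an AE". No exception is given for cause, body site, severity or relation to flare.
- **Study Design** describes a different population: "Adults with clinician-confirmed RA in remission who are undergoing or are about to begin DMARD tapering". The inclusion criterion in Textbox 2 is "DAS28-CRP)<2.4 at point of enrollment". Under **Delay to Final DAS28-CRP Calculation**, if a late CRP result lifts the baseline score above the remission threshold, "then the patient would become ineligible to continue and should be withdrawn from the study at this point".
- **Causality** says that all AEs should be "assessed by the principal investigator or their medically qualified delegate for any causal relationship with a study procedure", and it names activity monitoring among those procedures.
- **Clinical Discretion** accepts that joint findings can have causes other than RA. One of its examples is "trauma causing a painful or swollen joint".

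**The concern.** Two things are wrong. First, the safety section describes a population that the study does not recruit. Second, the AE exclusion covers symptoms by name, not by cause.

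The study procedure is long-term wrist wear. Each device is worn for 28 days and three are issued per period, which gives 3 × 28 = 84 days of wear. Periods may be repeated for up to 12 months if the ethics amendment is approved. The Causality section exists to find harm from that procedure. A wrist joint that becomes painful, swollen or stiff because of the device is a possible harm of it, yet the rule removes that event before causality is considered. What is at stake is one class of device-related harm in the safety tables of a pilot meant to inform a larger study.

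**Working it through.** No arithmetic applies. The point rests on wording, and the plan has no figure to reproduce. The passages are set side by side.

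**1. Population.**

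| Place | Disease state |
|---|---|
| Expected Symptoms | active RA |
| Study Design | remission |
| Textbox 2, inclusion criteria | DAS28-CRP below 2.4 |
| Delay to Final DAS28-CRP Calculation | withdrawn if the baseline score proves to be above the remission threshold |

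Three places agree and one contradicts them. Expected Symptoms is the one that is wrong.

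**2. Path of a wrist joint symptom caused by the device.**

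- The Adverse Event section defines an AE broadly enough to include it.
- Protocol Specifications then removes it, because it is joint pain, swelling or stiffness.
- Causality applies to AEs, so no assessment against the monitoring procedure is made.
- The Serious Adverse Event section defines an SAE as an AE with a serious consequence, so the symptom does not enter that definition either.
- Safety Outcomes tabulates AEs and SAEs, so the symptom cannot appear there.

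**3. Path of a joint symptom with another non-RA cause.** Under Clinical Discretion the investigator may discount the resulting rise in DAS28-CRP and treat the patient as in remission. Protocol Specifications then keeps the symptom out of AE recording. As a symptom it counts neither as flare nor as an AE. The underlying injury or infection is a separate diagnosis and can still be recorded. Fatigue with a non-RA cause is barred in the same way.

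**4. What the rule leaves recordable.** Skin irritation, rash or pressure marks from the strap are not on the list of four. They still meet the AE definition, get a causality assessment and are tabulated.

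**5. What the exclusion can properly rest on.** Ethical Considerations puts the risk of flare at about 50%, and Expected Symptoms itself mentions flare. That is a sound reason to keep symptoms of RA activity out of the AE record even in a remission cohort, because flare is captured as the study outcome. It is no reason to exclude joint symptoms or fatigue with another cause.

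**The case against.** **The exclusion does not need the active-RA phrase.** Protocol Specifications does not cite Expected Symptoms. The link is inferred from their adjacency and the identical list. Flare risk alone would justify excluding RA symptoms, and a composite score below 2.4 does not mean that a patient has no joint symptoms. This stands. Correcting the population description would leave the rationale for excluding RA symptoms largely intact. It would not supply a reason for excluding symptoms with other causes.

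**A carve-out is not a contradiction.** Causality concerns events that are AEs, and Protocol Specifications says which symptoms are not. This also stands: the two sections do not formally conflict. The defect is that the carve-out reaches symptoms that the causality assessment is meant to examine.

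**Other channels exist.** The feedback survey covers comfort, and joint counts and the weekly RA-FQ register joint symptoms. This is true, but the article describes no causality or severity grading for the survey, and the joint counts and RA-FQ do not attribute a symptom to the device. The survey's free text is also uncertain as a source: Patient Acceptability plans to look for themes in it, while Secondary Analyses says that it will not be analyzed.

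**Stronger readings that a reader might infer.** One is that no wrist effect of the device can be recorded. The documents do not support this, because non-joint effects remain AEs. Another is that the feasibility conclusion rests on the AE table and would therefore overstate tolerability. The documents do not support this either: acceptability is a secondary objective assessed by questionnaire, and nothing ties feasibility to the AE counts.

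**Conclusion.** Wrong as written; minor severity. The active-RA statement contradicts the remission requirement. The AE exclusion is too wide by the class of joint symptoms and fatigue not due to RA activity, which includes wrist joint symptoms caused by the device. Followed literally, that class is absent from the AE and SAE tables whatever its true frequency.

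The size cannot be put as a number. The documents give no rate of device-related joint symptoms, and an event type that is not collected is not an observed zero, so a confidence limit for zero events would be misplaced. Eligibility is governed by Textbox 2 and the baseline withdrawal rule, so the slip does not change who is recruited. No effect on the primary outcome, the prediction models or the sample size is shown.

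The conclusion assumes that site staff apply the exclusion as it is worded. This is a stated rule and not a detail left to a fuller document, so the condensed form of a journal article does not explain it.

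**What to change.** 1. In Expected Symptoms, describe the cohort as *patients with RA in remission, at risk of flare during tapering*.
2. In Protocol Specifications, limit the exclusion to joint pain, swelling, stiffness and fatigue judged to be due to RA activity.
3. Record as AEs, with causality, joint symptoms at the device site judged possibly device-related, and joint symptoms or fatigue attributed to a non-RA cause.

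The cost is protocol wording, a few extra AE form entries and an attribution judgment by the investigator. Clinical Discretion already asks for a similar judgment when an elevated DAS28-CRP is discounted. No visits are added and clinical management does not change. With 16 of the planned 100 participants recruited by July 1, 2026, up to 84 could be followed under the corrected rule from enrollment.

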#### Reporting AEs and SAEs

AEs and SAEs will be reported as follows:

*All AEs* will be recorded on AE case report forms at the research site.Site staff should report any *SAE immediately* to the chief investigator. Upon receipt of the SAE report, the chief investigator must:*All SAEs*: Immediately inform the Sponsor (within 1 working day)Inform the REC on behalf of the sponsor as soon as possible, and no later than 15 calendar days for nonfatal and non−life-threatening SAEs
*Unexpected SAEs related to a study procedure (suspected unexpected serious adverse reaction [SUSAR]):*
Inform the REC on behalf of the sponsor as soon as possible, and no later than 1 calendar day for fatal or life-threatening SAEs.Convene a meeting of the chief investigator and study investigators as soon as possible, and no later than:Fifteen calendar days for fatal or life-threatening SAEsThirty calendar days for nonfatal and non–life-threatening SAEs

#### Pregnancy

Pregnancy is associated with a diverse range of physiological changes and can therefore be expected to greatly influence physical activity data. Current pregnancy is an exclusion criterion because pregnancy-related physiological and behavioral changes may substantially affect physical activity and accelerometry-derived outcomes. If pregnancy is identified after enrollment, wearable monitoring and all further study-specific procedures will be discontinued, and the participant will be withdrawn from the study. The referring rheumatologist and general practitioner will be informed where clinically appropriate. Pregnancy will be documented and reported in accordance with sponsor safety-reporting requirements, and data collected before withdrawal will be retained and analyzed in accordance with the participant’s consent.

### Data Analysis

#### Preprocessing of Accelerometry Data

Axivity AX6 device data will be processed using established, standardized pipelines to derive quality metrics and daily summary metrics from the raw 3-dimensional acceleration and gyroscope signals, covering activity outcomes including volume (eg, step count), pattern (eg, distribution of activity across the day), and variability [20,21]; mobility outcomes including pace and rhythm variability [22]; and sleep outcomes including duration and sleep bouts, defined as interruptions [23].

#### Patient Acceptability

Quantitative feedback from patient acceptability questionnaire Likert scales will be summarized (median or mode and range). Anonymized free-text responses will be reproduced verbatim, analyzed for common themes, and presented in tabular form. The focus of these analyses is to gather information around patient acceptability for the purposes of improving the design of our future research studies, rather than to generate generalizable data and results suitable for a qualitative research publication [14,24].

### Statistical Analysis

#### Timing of Analyses

The main analysis will take place once follow-up has been completed for all participants and all data queries have been resolved, as far as possible.

#### Descriptive Analyses

##### Participant Baseline Characteristics, Clinical Measurements, and PROMs

Participant baseline characteristics, clinical measurements, and PROMs will be summarized based on the type of variable. Continuous variables will be described using appropriate summary statistics (eg, mean, SD and/or median, IQR, and range), and categorical variables will be presented as frequencies and percentages. Relevant plots will be generated to aid visualization.

##### RA-FQ

The RA-FQ is also designed to remotely monitor patients with RA during drug tapering. Participants rate, on a 0‐10 scale, their pain, difficulty with physical activities, fatigue, joint stiffness, and challenges in daily activities such as work, over the past week. At the end of the questionnaire, 2 yes or no questions ask whether the patient has experienced these symptoms for more than 1 week and whether they believe they are currently experiencing a flare of RA. The responses provide a standardized way to assess symptom severity and detect flares, helping clinicians track disease activity and adjust treatment if needed. The questionnaire will be collected weekly for each patient. For the 0‐10 scale items, the average score for each symptom will be calculated across all patients at 4 main visit time points, and summary statistics (eg, mean, SD, and/or median, IQR, and range) will be reported.

##### HAQ-DI Questionnaire

The HAQ-DI will be used to assess functional disability in patients with RA. It includes domains covering dressing and grooming, arising, eating, walking, hygiene, reach, grip, and activities or errands. Items are scored from 0 (no difficulty) to 3 (unable to do), with domain scores defined as the highest item score within each domain and adjusted for the use of aids or assistance according to standard scoring rules. The overall HAQ-DI score is calculated as the mean of domain scores (range 0‐3), with higher scores indicating greater disability. Scores will be summarized descriptively at each study visit using appropriate summary statistics (mean, SD, median, IQR, and range), and changes over time will be presented graphically.

##### Safety Outcomes

Safety outcomes, including AEs and SAEs, will be tabulated by type and severity, with the number and proportion of participants affected and the total number of occurrences reported.

### Primary Analyses

The primary outcome is the time from study enrollment to the first clinically confirmed RA flare, defined as a DAS28-CRP of 2.4 or above.

The primary objective of the study is to predict clinically confirmed flare risk using dynamic risk prediction methods based on daily accelerometry data including both the quality metrics and the physical activity measures. In addition, we would like to retrospectively assess the accuracy of the model vs patient-reported flare.

We will use landmarking models to develop a dynamic risk prediction approach for arthritis flare. Landmarking is a time-updated survival modeling framework that generates risk predictions at predefined time points (landmark times) using information available up to each time point. Predictions are then made over specified future time horizons.

The approach consists of two components:

A longitudinal submodel, which summarizes repeated accelerometry-derived measurements over timeA time-to-event submodel, which estimates the risk of flare from each landmark time

At each landmark time, the longitudinal submodel is used to extract summary measures of the accelerometry data up to that time, and these summaries are then included as predictors in the time-to-event model to estimate the future risk of flare.

The event of interest is the first clinically confirmed arthritis flare. Participants who do not experience a clinically confirmed flare will be censored at the end of their individual follow-up period or at earlier withdrawal.

For the time-to-event component, we will fit both Cox proportional hazards models and random survival forests (RSFs) to assess potential improvements in predictive performance and capture potential nonlinear relationships and interactions. We also consider including variables such as age, sex, Clinical Frailty Score, and anticitrullinated protein antibodies (ACPAs) antibody status (either positive/negative or the actual titer) as fixed effects or variables in both longitudinal and time-to-event submodels as they are clinically important.

The model will be generated at weekly landmark times throughout follow-up. At each landmark, the model will use all accelerometry data collected up to that time to estimate the probability of clinician-defined flare occurring within the subsequent 14 days. Weekly updating allows risk estimates to be refreshed throughout DMARD tapering and provides clinically actionable information to support decisions regarding continuation or modification of tapering.

We will also evaluate the accuracy of the model’s flare predictions for each prediction time window against patient-reported flares derived from the RA-FQ, based on responses to the yes or no question about current flare status. Patient-reported flare status will serve as the reference standard. Model-predicted flares will be compared against patient reports to calculate sensitivity, specificity, and agreement (Cohen κ). It helps to assess how well the model’s predictions align with patient perception.

Sensitivity: proportion of patient-reported flares that are correctly predicted by the model (true-positive rate); higher values, close to 100%, are desirable.Specificity: proportion of patient-reported nonflares that are correctly identified as no flare by the model (true-negative rate); higher values, close to 100%, are desirable.Agreement: measured using Cohen κ to quantify concordance between model-predicted and patient-reported flares; higher values, close to 1, indicate stronger agreement beyond chance.

